### Sample size

Large standardized effect sizes (e.g. 0.1-0.5 m stride length; 10-25 m/min gait speed) shown in previous experiments where there were 2 active interventions to improve gait in people with PD using strategy training [11] (Cohen's d >5) led to the prediction that a sample size of 30 in each group will yield power in excess of 99% with α = 0.05 for step length and speed. Previous studies with similar populations of people with PD (Morris [11,28,29,31] et al., indicate that attrition is typically in the range of 5-8%. Even if the sample diminished by 2 in each group, the power would still exceed 95%.

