## Background

Over 4 million people worldwide are estimated to be diagnosed with Parkinson disease (PD), with this projected to double within the next 20 years [1]. More than half of community dwelling adults living with PD experience gait disturbances that are associated with increased disease severity, disability, poor quality of life [2] and caregiver strain[3,4]. Falls are a common complication of PD, with between 50 and 68% of people with PD falling each year [5-8], with most falls reported to occur when walking [9]. Medications such as levodopa, provide the cornerstone of treatment of gait disturbances in PD, however these become less effective over time for some symptoms of PD including gait disturbance. There is growing evidence that strategy training, whereby internal or external cues are used to direct a person's attention to normalise their gait deficits, is effective in augmenting drug therapy to improve gait in the short term [10]. Internal cues involve the person directing their attention to consciously think of improving the deficit (e.g. thinking 'big steps'). External cues aim to normalise the gait deficit and often include verbal cues (e.g. saying 'big steps'), visual cues (e.g. lines on the floor at the desired step length) [11], or auditory cues (e.g. metronome to normalise cadence) [12]. The majority of this evidence is based on laboratory-based training [10] with low sample sizes, and measures of immediate effects of therapy. The longer term effect of strategy training is not yet clear.

For gait to be functional in daily life both within the community and home, people need to be able to dual task. This could involve thinking when walking or maintaining balance when holding an object. It is well known that performing an added task interferes with postural stability in older adults (termed dual task interference) [13], particularly in those adults with impaired balance [14-16].

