### Outcome measures

The primary outcome measure will be step length when dual tasking over 8 metres. Reduced step length has been shown to be one of the primary gait deficits in people with PD [31]. Participants will walk an unobstructed 10 metre path over an 8 metre GAITRite^® ^electronic walkway at a comfortable pace. At the same time, they will be asked to perform an added spoken task, including saying as many words as possible beginning with certain letters, termed the controlled oral word association test (words), or counting backwards by 3s beginning with a number between 50 and 100 (count). Both these tasks have been used to demonstrate altered gait in people with PD when dual tasking [20,25]. Step length is calculated by the GAITRite system, with the mean value used in analysis. The GAITRite^® ^system has demonstrated sensitivity to change in gait parameters in people with PD [32] and has been used as a gold standard comparator when investigating gait under dual task conditions in people with PD [33]. Assessment will be performed during the patient's self-reported optimal 'ON' period, often 1 hour post medication.

Secondary outcome measures include: spatiotemporal gait parameters when walking under single and dual task conditions, cognitive function, functional gait performance, community mobility, and quality of life. Spatiotemporal gait parameters other than step length will be recorded when walking at a comfortable pace over 10 metres under both gait only (single task) and the two dual task conditions detailed previously. These will include gait speed (m/s), cadence (steps/min), stride length (m), step length coefficient of variation (CV) and double support time (s).

Cognitive domains to be tested by a neuropsychologist include: executive function, attention, visual perception and processing speed. Tests have been selected based on their ability to assess the required domains, and their ability to detect deficits in the Parkinson Disease population [34]. Tests include the Trail making A & B Tests [35]; the Stroop colour-word interference test [36], and a Digit span test [37].

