### Data analysis

Data analysis will be performed on an intention-to-treat basis using an alpha level of 0.05. Descriptive statistics will be used to ensure comparability of scores between groups at baseline, to describe performance at each phase and to test whether the assumptions for use of parametric statistics have been met. If the assumptions for F or t-tests are violated, equivalent non-parametric statistics will be utilized. The main hypothesis will be tested using General Linear Models (repeated measures analysis of variance, ANCOVA), in a 2 group (single task, dual-task) × 4 phase (baseline 1, baseline 2, post intervention, follow up) model. This will be followed by between-groups planned comparisons using the t-statistic. All secondary outcomes will be analysed in a similar manner. Disease duration and age will be used as co-variates in all analyses. Data will be analysed using SPSS.

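### The stated power (>99% with 30 per group, >95% with 28) rests on a Cohen's d above 5 that the protocol does not support for the between-arm difference in dual-task step length

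*Protocol article*

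**What the plan says.** All of the following is in the protocol article.

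- **Sample size, effect:** the starting point is "Large standardized effect sizes (e.g. 0.1-0.5 m stride length; 10-25 m/min gait speed"), attributed to earlier experiments with two active interventions "using strategy training [11] (Cohen's d >5").
- **Sample size, power:** these effects "led to the prediction that a sample size of 30 in each group will yield power in excess of 99" per cent, at alpha 0.05, for both step length and speed. After attrition: "Even if the sample diminished by 2 in each group, the power would still exceed 95" per cent. No SD is given.
- **Outcome measures:** "The primary outcome measure will be step length when dual tasking over 8 metres".
- **Data analysis:** a 2-group by 4-phase repeated-measures model, then planned between-group t comparisons, with age and disease duration as covariates. "Data analysis will be performed on an intention-to-treat basis using an alpha level of 0.05"; sidedness is not stated.
- **Intervention:** both arms have 12 one-on-one sessions directed at step length. The dual-task arm uses the external cueing described for the single-task arm and adds concurrent tasks.
- **Background:** on strategy training, "The majority of this evidence is based on laboratory-based training [10] with low sample sizes, and measures of immediate effects of therapy".
- **Discussion:** no earlier trial is said to have compared these two forms of training.

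**The concern.** A power statement is only as good as its effect size, and here one value carries everything. It comes from other interventions and is illustrated by outcomes other than the primary one. The contrast in this trial is the increment from adding tasks to training that both arms largely share. If nobody has made the comparison before, no observed d exists for it.

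What is at stake is how a null result is read. The Discussion promises clear evidence on whether dual-task training should be advocated. Beside a claim of more than 99% power, a non-significant difference would be taken as near proof that the two trainings are equivalent, although a moderate benefit of either could have been missed.

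**Working it through.** **Inputs.** From the protocol: alpha 0.05, 30 per group (28 after the stated loss), 1:1 allocation, d above 5, stride difference 0.1 to 0.5 m, speed difference 10 to 25 m/min. Assumed: two-sided test, unadjusted two-sample t-test. Every d below 5, every SD and every correlation used below is also an assumption, because the protocol gives none.

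**Formula.** Power = P(|T| > t(0.975; 2n − 2)), where T is noncentral t with 2n − 2 degrees of freedom and noncentrality d√(n/2).

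**1. The plan's own figures.** At d = 5 the noncentrality is 5 × √15 = 19.4 with 30 per group and 5 × √14 = 18.7 with 28. Power is 1.000 in both cases, so both stated lower bounds are met.

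**2. What d = 5 would require.** With 3 per group the noncentrality is 5 × √1.5 = 6.12, the critical value on 4 degrees of freedom is 2.78, and power is 99.3%. A d above 5 therefore cannot be what led to 30 per group.

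**3. What d above 5 implies about spread.** SD = difference / d.
- Stride: below 0.1/5 = 0.02 m at the low end, below 0.5/5 = 0.10 m at the high end.
- Speed: below 10/5 = 2 m/min to below 25/5 = 5 m/min.

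A stride SD below 0.02 m is hard to credit as a between-person SD in a sample spanning Hoehn and Yahr stages I to IV.

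**4. Power at other effect sizes.**

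| Assumed d | 30 per group | 28 per group |
|---|---|---|
| 0.3 | 21% | 20% |
| 0.5 | 48% | 45% |
| 0.8 | 86% | 84% |
| 1.0 | 97% | 96% |

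**5. Smallest d for a given power, unadjusted.**

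| Per group | 80% | 90% | 99% |
|---|---|---|---|
| 30 | 0.74 | 0.85 | 1.13 |
| 28 | 0.76 | 0.88 | 1.17 |
| 27 | 0.78 | 0.90 | 1.19 |

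**6. In metres, 30 per group, over a range of assumed step-length SDs.**

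| Assumed SD (m) | Power, 0.05 m difference | Power, 0.10 m difference |
|---|---|---|
| 0.05 | 97% | 100% |
| 0.08 | 66% | 99.7% |
| 0.10 | 48% | 97% |
| 0.15 | 25% | 72% |

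**7. With baseline adjustment.** Suppose the analysis adjusts for the mean of the two baselines and all pairs of visits correlate at r. The residual SD then shrinks by √(1 − 2r²/(1 + r)):
- r = 0.5: √(1 − 0.5/1.5) = 0.816. The d needed with 30 per group is 0.736 × 0.816 = 0.60 for 80% power and 1.126 × 0.816 = 0.92 for 99%.
- r = 0.8: √(1 − 1.28/1.8) = 0.537. The d needed is 0.736 × 0.537 = 0.40 for 80% power and 1.126 × 0.537 = 0.61 for 99%.

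**The case against.** The strongest reply is that nothing has been miscalculated. Given d = 5, both bounds are true. The earlier experiments are said to have compared two active interventions, which is the plan's reason for thinking them relevant, and they cannot be inspected here. The Background's remark about small studies of immediate effects describes most of the evidence, not necessarily the cited experiment. Power of 99% does not need d = 5 at all: about 1.13 is enough. The planned model also uses two baselines, so unadjusted figures may understate its power.

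Most of this stands, and it limits the point. Some stronger readings are tempting but not supported:

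- A reader might infer that the trial lacks the power it claims, or that d above 5 is impossible. The true d and SD are not in the document, so neither is shown.
- A reader might see a conflict between the 99% and 95% figures. Both are lower bounds, so they are compatible, although at d above 5 the loss of 2 per group would change nothing.
- A reader might argue that a step, being roughly half a stride, halves the effect. The difference and its SD would shrink together, leaving d unchanged.
- A reader might object to the attrition allowance. A loss of 2/30 = 6.7% lies within the stated 5-8%.

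The reply does not supply a reason to carry d above 5 over to this contrast. Two active interventions elsewhere are not these two, which share their cueing and step-length training. Baseline adjustment helps, but the Data analysis section names only age and disease duration as covariates. Even with adjustment, 99% power would need d of about 0.61 to 0.92 at the assumed correlations, and the document offers no evidence for an effect of that size.

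**Conclusion.** The point holds as a matter of unsupported input, not of arithmetic. The two power figures depend wholly on a standardised effect that the protocol does not tie to dual-task step length, to these two arms, or to a stated SD, and that could not have produced the chosen sample size. The claimed power is unsupported and likely overstated.

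The size of any shortfall is conditional. On an unadjusted two-sided test with 30 per group, the claim is true only if the between-arm d is at least 1.13. For assumed d from 0.3 to 0.8, power is 21% to 86%. For an assumed step difference of 0.05 m, it runs from 97% down to 25% as the assumed SD rises from 0.05 to 0.15 m. This is not detail left to a fuller document: the article itself states the effect size, the sample size and the power.

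**What to change.** Keep 60 participants and rewrite the Sample size paragraph:

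1. Delete the d above 5 and both power percentages.
2. State the detectable between-arm difference in dual-task step length. Unadjusted, 80% power: d = 0.74, 0.76 and 0.78 with 30, 28 and 27 per group. Unadjusted, 90% power: 0.85, 0.88 and 0.90.
3. If the analysis will adjust for the mean of the two baselines, say so and give the matching figure: d of about 0.60 to 0.40 for 80% power with 30 per group, for an assumed correlation of 0.5 to 0.8.
4. Convert the chosen d to metres with a cited between-person SD of dual-task step length, and state that the test is two-sided.
5. Add that a non-significant result will be interpreted from the confidence interval for the between-arm difference, not from the planned power.

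The cost is one reworded paragraph and a less favourable stated power. No extra participants are needed.

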### Ethics approval

The study protocol has been approved by the University of Queensland Medical Research Ethics Committee (MREC ID: 2007001631), the Princess Alexandra Hospital Ethics committee (ID: 2009013), the Uniting Care Health Human Research Ethics Committee (ID: 0911).

## Discussion

This trial will be the first to compare the effect of dual task training when walking with single task (usual strategy gait training) in people with PD. Currently it is not clear whether training dual tasking when walking should be advocated in people with PD. It will measure the effect on not only gait performance, but also on other indicators of impairment, activity and participation both immediately following training, and for a follow up period of 6 months. This data will assist in determining the impact of physiotherapy gait training for people with Parkinson Disease who are still mobile and living in their own homes. It will be one of the first studies to monitor the effect of this type of intervention on community mobility disability in the PD population, and to determine transference to activities in daily life.

Findings from this study will provide insights into the effects of practice on dual-task performance in people with PD. It will generate new knowledge regarding optimal principles of training to enable people with PD to overcome debilitating dual task interference during rehabilitation. The information gained from this project has the potential to change the way gait training is structured, and will provide clear evidence as to whether dual task training should be advocated in people with PD. Our results are likely to have wider implications for training other populations who commonly demonstrate dual task interference with postural tasks such as elders [14,15] and people with brain injuries [16] as it is expected that the principles underpinning the design of the training program will be transferable to these populations.

## List of abbreviations

PD: Parkinson's Disease; RCT: Randomised Controlled Trial; MMSE: Mini Mental Status Examination; CV: Co-efficient of Variation; TUG: Timed Up and Go; ICC: Intraclass Correlation Coefficient; EQ-5D: EuroQuol; PDQ-39: Parkinson's Disease Questionnaire-39; UPDRS: Unified Parkinson's Disease Rating Scale; ANCOVA: Analysis of Covariance; SPSS: Statistical Processes for the Social Sciences.
